## Abstract

**Background:**

Recent research indicates that 35 percent of blue-collar workers in the US currently smoke while only 20 percent of white-collar workers smoke. Over the last year, we have been working with heavy equipment operators, specifically the Local 324 Training Center of the International Union of Operating Engineers, to study the epidemiology of smoking, which is 29% compared to 21% among the general population. For the current study funded by the National Cancer Institute (1R21CA152247-01A1), we have developed the Tobacco Tactics website which will be compared to the state supported 1-800-QUIT-NOW telephone line. Outcome evaluation will compare those randomized to the Tobacco Tactics web-based intervention to those randomized to the 1-800-QUIT-NOW control condition on: a) 30-day and 6-month quit rates; b) cotinine levels; c) cigarettes smoked/day; d) number of quit attempts; and e) nicotine addiction. Process evaluation will compare the two groups on the: a) contacts with intervention; b) medications used; c) helpfulness of the nurse/coach; and d) willingness to recommend the intervention to others.

**Methods/Design:**

This will be a randomized controlled trial (N = 184). Both interventions will be offered during regularly scheduled safety training at Local 324 Training Center of the International Union of Operating Engineers and both will include optional provision of over-the-counter nicotine replacement therapy and the same number of telephone contacts. However, the Tobacco Tactics website has graphics tailored to Operating Engineers, tailored cessation feedback from the website, and follow up nurse counseling offered by multimedia options including phone and/or email, and/or e-community. Primary Analysis of Aim 1 will be conducted by using logistic regression to compare smoking habits (e.g., quit rates) of those in the intervention arm to those in the control arm. Primary analyses for Aim 2 will compare process measures (e.g., medications used) between the two groups by linear, logistic, and Poisson regression.

**Discussion:**

Dissemination of an efficacious work-site, web-based smoking cessation intervention has the potential to substantially impact cancer rates among this population. Based on the outcome of this smaller study, wider scale testing in conjunction with the International Environment Technology Testing Center which services Operating Engineers across North America (including US, Mexico, and Canada) will be conducted.

**Trial registration:**

NCT01124110

## Background

Blue-collar workers are at significant risk for cancer in that 35 percent are current smokers compared to 20 percent of white-collar workers [1]. Blue-collar workers are less likely to use proven tobacco cessation treatments compared to those of higher socioeconomic status (SES) [2]. In addition, blue-collar workers do not benefit from worksite smoking bans and restrictions. While there is an understanding of factors that contribute to elevated tobacco use in blue-collar workers, little research has focused on cessation. The data available suggests that developing novel approaches of disseminating efficacious interventions may be effective in reducing tobacco-related disparities and cancer among blue-collar workers [3].

Our preliminary data show that smoking rates are high among the Local 324 Training Center of the International Union of Operating Engineers at 29% compared to 21% among the general population [4]. The good news is that over half of the tobacco users reported that they are interested in quitting. With funds from the Department of Veterans Affairs (VA) and Blue Cross/Blue Shield of Michigan Foundation, we have built and pre-tested a Tobacco Tactics website and the results are promising. Hence, this funded National Cancer Institute R21 for Exploratory Grants for Behavioral Research in Cancer Control (1R21CA152247-01A1) is a randomized control trial (RCT) to test the Tobacco Tactics website intervention compared to the 1-800-QUIT-NOW quit line. The specific aims are to: Aim 1: Compare the efficacy of the Tobacco Tactics website intervention to the state sponsored 1-800-QUIT-NOW telephone line in improving cessation including: a) 30-day and 6-month quit rates; b) cotinine levels; c) cigarettes smoked/day; d) number of quit attempts; and e) nicotine addiction. Aim 2: Compare Operating Engineers randomized to the Tobacco Tactics website to those randomized to the 1-800-QUIT-NOW telephone quit line in terms of: a) contacts with the intervention; b) medications used; and c) helpfulness of the nurse/coach; and d) willingness to recommend the intervention to others (5 point scale ranging from strongly disagree to strongly agree).

### Risk of smoking among operating engineers

Among workers in dusty occupations, smoking is particularly detrimental to health because of the synergistic effect with occupational exposures which place workers at additional risk for respiratory disease [5]. Operating Engineers, those who operate heavy earth moving equipment, are particularly at risk for cancers of the lung [6], head and neck [7], and trachea and bronchus [8]. Since most Operating Engineers are men, unlike women, they may not seek regular health care. Yet even when seen by a health care provider, only 53% of construction workers were advised to quit smoking [9]. Given the high rates of smoking, the interaction between smoking and respirable dust exposure which enhances cancer rates, and lack of access to cessation interventions, an efficacious worksite smoking cessation intervention has the potential to substantially impact the health of Operating Engineers by reducing cancer rates.

### Cessation interventions

Countless RCTs have shown that cessation interventions that include both behavioral counseling and medications (nicotine replacement therapy and/or bupropion, or varenicline) are efficacious and produce quit rates ranging from 15–35% [10,11]. Studies have shown that the 1-800-QUIT-NOW telephone counseling programs offered in 48 states are efficacious although few smokers are reached [12]. A Cochrane Review of work site interventions concluded that group programs and nicotine replacement therapy increase quit rates, however, participation rates are low [13] .Only one worksite web-based intervention was found whereby 1,776 IBM employees were provided with the commercial QuitNet site showing a 43% quit rate among responders (13% intention-to-treat quit rate) [14], but this study did not include blue-collar workers, those most at risk for smoking.

Reports suggest that over 70% of all adults in the US are connected to the internet [15], 9.6 million blue-collar workers use the internet, and blue-collar workers are interested in computer technology [16]. While many smoking cessation websites are already available, many users encounter frustrations on sites which are poorly designed [17-19]. A Google search for “quit smoking” did not reveal some of the most efficacious cessation websites. Despite multiple design and informational problems, web-based cessation interventions have been shown to reduce tobacco use [20-23], be more efficacious than self-help booklets [24], be more efficacious if they provide tailored messages [25,26], and can enhance quit rates in conjunction with nicotine replacement therapy [24,25,27,28]. Thus far, no studies have compared web-based cessation interventions to the 1-800-QUIT-NOW telephone line.

Web-based interventions can also be enhanced with provider email or telephone contact [29]. A Cochrane Review meta-analysis showed that cessation advice by nurses increased the likelihood of quitting compared to advice without nurse counseling [30]. Studies have also shown that telephone counseling for cessation is efficacious [31,32]. Thus far, nurse-moderated web-based interventions have not been tested.

### Development of the Tobacco Tactics website for operating engineers

The efficacy of the face-to-face Tobacco Tactics intervention was tested among head and neck cancer patients in a published RCT and the face-to-face component has been disseminated to all inpatient smokers at two Veterans Affairs (VA) Hospitals compared to a control hospital [33]. Social marketing techniques were used to develop the image-based VA Tobacco Tactics program logo and campaign character [34]. Based on the face-to-face intervention, the Tobacco Tactics website was developed and pre-tested in the VA. Having found that smoking rates are high among Operating Engineers, we received a grant from the Blue Cross/Blue Shield of Michigan Foundation to redesign the Tobacco Tactics website for Operating Engineers.

### Theoretical framework

As in our prior studies, the theory guiding the Tobacco Tactics website intervention is the Health Belief Model [35]. This model proposes that behavior is influenced by Perceived Benefits (e.g., effectiveness of quitting smoking to reduce health risk and financial benefits), Perceived Barriers (withdrawal symptoms and other obstacles to quitting), Self-Efficacy (feeling of confidence that one can quit), Cues to Action (stimulus and reminders), by Perceived Susceptibility (chance of having negative health outcomes if continuing to smoke), and Severity of the Health Threat. Our current research has demonstrated that these characteristics are associated with 6-month quit rates and quit attempts.

## Methods

### Design

The design for this two year study will be a RCT. The experimental group will receive the Tobacco Tactics website intervention. The control group will receive the 1-800-QUIT-NOW telephone quit line. Data on tobacco use will be collected at baseline, 30-day, and 6-month follow-up. See Figure 1 for a Consolidated Standards of Reporting Trials (CONSORT) diagram [36]. Institutional Review Board approval has been received from the University of Michigan.

**Figure 1 F1:**
[figure not shown]
Experimental Design Overview.

### Setting/sample/power analysis

#### Setting

One of the greatest strengths of this proposal is the “buy in” that we have from leadership at the Local 324 Training Center of the International Union of Operating Engineers. While leadership has always been interested in the health of their workers, as evidenced by their prior participation in hearing protection studies, this “buy in” is even greater now that the trend in Michigan is to shift health care costs to unions [37,38]. Michigan Operating Engineers are required to attend annual safety training generally conducted at a centralized education center in Howell, MI. Some of the safety training is conducted face-to-face and some is conducted on the computer. Hence, we have worked with the Local 324 Training Center of the International Union of Operating Engineers to integrate the web-based Tobacco Tactics intervention into their annual safety training.

#### Sample

Inclusion criteria in this study are Operating Engineers who: 1) are attending a safety training course provided by Local 324 Education Center; 2) are greater than 18 years of age; 3) currently smoke; and 4) are interested in participating in a cessation program. A prior sample from this population has been described in another study [39]. In brief, the mean age was 43 (range18–70 years), most were male (92%), white (92%), married (68%), had a high school education or less (61%), and (29%) were current tobacco users.

#### Power analysis

For Aim 1, power analysis conducted with Power Analysis and Sample Size software (PASS) indicated that the sample size of 92 per group would provide 80% power to detect a 16% difference [33] in quit rates with alpha of .05 two tailed. For Aim 2 which will test of differences in means between the two groups, there will be 92% power to detect what Cohen [40] described as a medium sized difference when tested with alpha of .05, two tailed. Since Local 324 services about 16,000 Operating Engineers and about 29% smoke, we expect that we can easily recruit the 184 smokers needed for this study. To date 135 Operating Engineers have been randomized and recruitment and follow-up is ongoing.

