#### Randomization and access to the intervention

Since there is a high probability for cross-contamination within training sessions, randomization will occur by training group (all individuals attending a specific training will be randomized to the same arm). The instruction sheet will give them information for logging on to the Tobacco Tactics website or calling the 1-800-QUIT-NOW telephone quit line. All subjects will be given time to make this first contact with the intervention during the training session where they will have access to a computer or telephone. After participating in the web-based Tobacco Tactics intervention, participants may continue to access the website from home, but this is not necessary as repeated access has not always been shown to increase efficacy of web-based interventions [25]. Both the intervention and control group will receive follow-up telephone calls. Both interventions are described in detail below.

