### Data analysis

The equivalence of the two groups will be tested using *χ*^2^ tests of association for categorical variables and t-tests for quantitative variables. Variables on which the groups differ will be included as covariates in the analyses. Clustering by group will be accounted for in analysis by using Generalized Linear Mixed Model variations of logistic regression, linear regression, and Poisson regression [56]. Analyses of all aims will be conducted by two-tailed tests with alpha of .05. An intent-to-treat approach will be used so that subjects are considered to be in the condition to which they were randomized despite how much they actually used that type of care.

The primary focus for Aim 1 is on comparing the two interventions (Tobacco Tactics website and 1-800-QUIT-NOW control condition) in their effects on smoking cessation using 6-month self-report together with results of the 6-month cotinine test. Using an intent to treat analysis, participants who cannot be reached or who fail to return the cotinine strip will be considered to be still smoking. Analysis of this measure will be conducted by using logistic regression of quit rate adjusted for clustering to compare the quit rates of those in the intervention arm to those in the control arm. Percentage quitting by group will be presented as a descriptive statistic to characterize the difference in quit rates between the two groups. This analysis will be supplemented by logistic regressions with smoking status as the dependent measure, treatment group as the independent variable, adjusted for clustering, but also adding in any baseline measures that were found in preliminary analyses to differ between groups, power permitting. If baseline measures differ between groups, we will effectively equate the groups. The same kinds of clustered logistic regression analyses will also be conducted on a less definitive version of the outcome measure: the self-report whether or not it is confirmed by a cotinine test. This analysis has the advantage of a slightly larger number of quitters identified because some people who actually quit smoking may not want to send in a urine sample (even on a cotinine test strip) because they fear it might reveal other problems.

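### The stated power (80% for Aim 1, 92% for Aim 2) shows no allowance for randomising whole training sessions, and the Aim 1 figure cannot be checked without a control quit rate

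*Protocol article*

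**What the plan says.** Under Power analysis, the article states for Aim 1 that "the sample size of 92 per group would provide 80% power to detect a 16% difference" "in quit rates with alpha of .05 two tailed". For Aim 2, which compares means, it states that "there will be 92% power to detect what Cohen [40] described as a medium sized difference" at the same alpha. The recruitment target is twice 92 with nothing added: "we expect that we can easily recruit the 184 smokers needed for this study". The paragraph gives no control quit rate, number of sessions, session size, ICC, design effect or response rate.

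Under Randomization and access to the intervention, allocation is by session: "randomization will occur by training group (all individuals attending a specific training will be randomized to the same arm". The reason given is contamination: "Since there is a high probability for cross-contamination within training sessions".

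Under Data analysis, the planned tests allow for this: "Clustering by group will be accounted for in analysis by using Generalized Linear Mixed Model variations". The same section counts people who are not reached, or who return no cotinine strip, as still smoking in the primary Aim 1 analysis.

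**The concern.** The design and the analysis treat the training session as a cluster, but the power paragraph appears to treat the 184 smokers as independent. If outcomes within a session are positively correlated, a mixed model works with less information than 184 independent people supply, and power falls below the stated values.

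This matters for how the result is read. A non-significant primary comparison would be judged against 80% power, and the Discussion makes wider testing depend on the outcome of this study. The article does not leave the matter to a fuller document: it reports sample size, power, effect, alpha and software as the trial's properties.

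**Working it through.** **Inputs from the article.** 92 per arm; two-sided alpha 0.05; a 16-point difference (Aim 1); a medium standardised difference, taken as d = 0.5 (Aim 2).

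**Inputs that are assumed.** Control quit rate, ICC and consenting smokers per session (m), because none is stated.

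**Step 1: reproduce Aim 2.** For a two-sample t-test the noncentrality is d√(n/2) = 0.5 × √46 = 3.391 on 182 degrees of freedom. Power is 92.1%, which is the printed 92%. The match uses 92 independent, complete observations per arm.

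**Step 2: try to reproduce Aim 1.** With p̄ the mean of p1 and p2, power = Φ{[Δ√n − 1.96√(2p̄(1−p̄))] / √(p1(1−p1) + p2(1−p2))}. For 10% v 26% this is Φ{(1.535 − 1.065)/0.531} = Φ(0.884) = 81.2%. Other control rates, with 92 per arm, a 16-point difference and no clustering:

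| Control rate | Power |
|---|---|
| 5% | 90.4% |
| 8% | 84.7% |
| 10% | 81.2% |
| 10.7% | 80.0% |
| 13% | 76.4% |
| 15% | 73.6% |
| 35% | 59.3% |

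Under Cessation interventions, the article reports 13% by intention to treat in one worksite web study, and says that counselling with medication can "produce quit rates ranging from 15–35" percent. At all of these rates, power is below 80% before any clustering.

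**Step 3: add clustering.** Design effect DE = 1 + (m − 1) × ICC, and effective n per arm = 92/DE. For m = 10 and ICC 0.05, DE = 1.45 and effective n = 63.4. Aim 1 at 10% v 26% is then Φ{(1.274 − 1.065)/0.531} = 65.3%. Aim 2 has noncentrality 0.5 × √31.7 = 2.82 and power 79.8%.

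| m | ICC | DE | Effective n per arm | Aim 1, 10.7% v 26.7% | Aim 1, 10% v 26% | Aim 2, d = 0.5 |
|---|---|---|---|---|---|---|
| 1 | any | 1.00 | 92 | 80.0% | 81.2% | 92.1% |
| 3 | 0.01 | 1.02 | 90.2 | 79.2% | 80.4% | 91.6% |
| 5 | 0.02 | 1.08 | 85.2 | 76.9% | 78.1% | 90.1% |
| 5 | 0.05 | 1.20 | 76.7 | 72.4% | 73.6% | 86.8% |
| 10 | 0.05 | 1.45 | 63.4 | 64.0% | 65.3% | 79.8% |

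These figures assume equal session sizes and ignore the limited number of sessions. With m = 10 there are about 184/10 ≈ 18 sessions. Testing on about 16 degrees of freedom lowers the last Aim 2 figure to about 75%.

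At a 10% control rate, the difference detectable with 80% power is 15.7 points without clustering, 16.5 points with m = 5 and ICC 0.02, and 19.6 points with m = 10 and ICC 0.05.

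**Step 4: survey non-response, Aim 2 only.** Suppose 75% respond (assumed), so 0.75 × 92 = 69 per arm and m shrinks in proportion.
- m = 5, ICC 0.02: DE = 1 + 2.75 × 0.02 = 1.055, effective n = 65.4, power 81.0%.
- m = 10, ICC 0.05: DE = 1 + 6.5 × 0.05 = 1.325, effective n = 52.1, power 71.5%.

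**The case against.** **Aim 1 is inferred, not shown.** Solving for the control rate that gives 80% and then calling the figure reproduced is circular. At 5% v 21%, 80% power needs 69 per arm, so 92 could absorb a design effect of 92/69 = 1.33. At 8% v 24% it needs 82, leaving room for 92/82 = 1.12. This stands. A reader might infer that the 80% has been proved to be an individual-randomisation figure, but the article does not establish that. It does make a hidden allowance unlikely: the comparator is an active treatment, the cited quit rates are all above 10.7%, and the companion Aim 2 figure has no allowance.

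**Loss to follow-up.** A reader might also infer that both figures assume complete follow-up. For Aim 1 the documents do not support this, because missing-as-smoking keeps all 184 in the analysis. Loss could still dilute the 16-point difference, but only if that figure is not already on a missing-as-smoking basis, and the article does not say. For Aim 2 the point holds for survey-based measures. The article does plan a mailed survey for online non-completers and gift cards of up to $50 in total, and website sign-ons are unlikely to depend on survey return.

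**The loss may be small.** About 29% smoke and over half of tobacco users are interested in quitting. Taking one half, about 0.29 × 0.5 = 14.5% of attendees are candidates. If all of them consented, 5 to 10 per session would imply about 34 to 69 attendees. Session size is not stated, so this does not exclude 5 to 10, but smaller clusters are plausible. With 3 per session and ICC 0.01, about 1 point is lost.

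**The analysis is sound on this point.** The mixed models address clustering, so the type I error and the effect estimate are not in question. Only the stated power is.

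**Conclusion.** The power paragraph is wrong as written for the design that the article describes. For Aim 2 this is demonstrated: 92% is the figure for independent, complete observations, and the trial has it only if the ICC is zero or each session supplies one smoker, and everyone responds. For Aim 1, the missing clustering allowance is a strong inference, and the 80% cannot be verified until a control quit rate is given.

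The size of the shortfall cannot be fixed from the document. Over the assumed grid (3 to 10 smokers per session, ICC 0.01 to 0.05), Aim 1 power goes from about 1 point below its starting value to 65% (10% v 26%), and Aim 2 power from 91.6% to about 80%. Non-response lowers Aim 2 further for survey-based measures. It would go too far to conclude that the trial is known to be badly underpowered: the low figures are one corner of that grid.

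**What to change.** Keep N = 184 and rewrite the Power analysis paragraph for a cluster-randomised design. State:

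- the assumed control quit rate behind the 16-point difference, and whether the rates count missing participants as smokers;
- the number of sessions, and the mean and coefficient of variation (CV) of consenting smokers per session, taken from the 135 already randomised without reference to arm or outcome;
- power and detectable difference for both aims over an ICC range, for example 0.01 to 0.05, using DE = 1 + [(1 + CV²)m − 1] × ICC so that unequal sessions are covered;
- the assumed survey response for the Aim 2 measures that depend on it.

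The cost is a short recalculation and a revised paragraph. No participants are added and no analysis step changes. The downside is that the stated power becomes less favourable.

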### Procedures

#### Recruitment and pre-intervention survey

During a regularly scheduled safety training session, the study nurse will describe the study to participants who are told that it is voluntary. Those interested will be directed to a separate room and provided with an information pack which includes: 1) an introductory information letter; 2) consent form; 3) instructions for completing the baseline survey; and 4) instructions for accessing the intervention to which the session has been randomized. If they have any questions a member of the research team will be available.

If they choose to participate, they will sign one copy of the consent form and return it to the study team. Participants in both arms will be directed to an online baseline survey on Qualtrics, with questions about their tobacco use and other covariates described below. One of the questions will ask for the identification number on the participants’ handout to link the subject with their survey without storing personal identifiers.

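### The arm is disclosed in the pack handed out before consent and the baseline survey, so signing up and baseline answers can depend on the arm

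*Protocol article*

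**What the plan says.** The order of events comes from two subsections under Procedures in the protocol article.

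- **Allocation.** Under Randomization and access to the intervention, "randomization will occur by training group (all individuals attending a specific training will be randomized to the same arm").
- **Recruitment.** Under Recruitment and pre-intervention survey, the nurse first describes the study. Then: "Those interested will be directed to a separate room and provided with an information pack which includes: 1) an introductory information letter; 2) consent form". The same pack also holds the baseline-survey instructions and "instructions for accessing the intervention to which the session has been randomized".
- **Consent.** The next paragraph opens: "If they choose to participate, they will sign one copy of the consent form and return it to the study team".
- **Baseline.** After that, "Participants in both arms will be directed to an online baseline survey on Qualtrics, with questions about their tobacco use and other covariates described below".
- **What the sheet reveals.** "The instruction sheet will give them information for logging on to the Tobacco Tactics website or calling the 1-800-QUIT-NOW telephone quit line".

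The Data analysis section tests the groups for baseline equivalence and states: "Variables on which the groups differ will be included as covariates in the analyses". For Aim 1, the main model is a logistic regression of 6-month quitting adjusted for clustering. Covariates on which the groups differ enter a supplementary model, if power allows. Intent-to-treat keeps enrolled subjects in their assigned arm.

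**The concern.** When clusters are randomized before individuals are recruited, randomization protects the comparison only if recruitment does not depend on the arm. Here a worker can read which program the session has been given and then decide whether to sign. If the website and the telephone line appeal to different kinds of smoker, the arms can differ in readiness to quit before any treatment starts, and the 6-month comparison would carry that difference.

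A second, lesser route is the baseline survey. It is self-reported and follows disclosure, so answers later used for adjustment may themselves be influenced by the arm.

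**Working it through.** The plan gives no figure on this point, so there is none to reproduce. The check is of sequence first, then of scale on assumed numbers.

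**Sequence**

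1. The wording of the pack's contents puts randomization of the session in the past, so allocation comes before the handout.
2. The consent form and the arm's access instructions are items in one pack.
3. The instruction sheet identifies the arm, because it tells the reader either to log on to the website or to call the quit line.
4. Choosing to participate and signing are described after receipt of the pack, and the survey after signing.
5. No sentence says that the sheet is sealed, withheld or handed over separately.

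Steps 1 to 5 leave the decision to sign, and the survey answers, open to knowledge of the arm.

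**What the analysis can repair**

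- Intent-to-treat applies to enrolled subjects. A worker who declines after seeing the sheet never enters either denominator.
- Baseline testing and adjustment reach only variables that were measured and found to differ, and those were reported after disclosure.
- The smoking-reduction models take baseline measures directly as covariates, so the survey route bears on them more than on the main quit-rate model.

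**Scale (assumed figures, not from the documents)**

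Suppose that treatment has no effect, and that quit rates are 30% in more motivated and 10% in less motivated smokers. If the motivated shares among those who sign are a and b in the two arms, then

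false difference = (0.30 − 0.10) × (a − b) = 0.20 × (a − b).

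The chance of a significant result in favor of the arm with more motivated joiners is approximately Φ[(difference − 1.96 × SE0) / SE1]. Here n = 92 per group (Power analysis section) and SE0 = √(2 × 0.20 × 0.80 / 92) = 0.0590. SE1 is the unpooled standard error. Clustering is ignored.

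| Motivated share, a vs b | Quit rates | False difference | Share of the 16-point target | Chance of significance in that direction |
|---|---|---|---|---|
| 50% vs 50% | 20% vs 20% | 0 points | 0% | 2.5% |
| 55% vs 45% | 21% vs 19% | 2 points | 12.5% | about 5% |
| 60% vs 40% | 22% vs 18% | 4 points | 25% | about 10% |
| 70% vs 30% | 24% vs 16% | 8 points | 50% | about 27% |

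For the third row, 0.60 × 0.30 + 0.40 × 0.10 = 0.22 and 0.40 × 0.30 + 0.60 × 0.10 = 0.18. Then SE1 = √[(0.22 × 0.78 + 0.18 × 0.82) / 92] = 0.0589, and Φ[(0.04 − 1.96 × 0.0590) / 0.0589] = Φ(−1.28) = 0.10. A 5-point gap in the shares would give only 0.20 × 0.05 = 1 point.

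**What can still be protected**

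The Power analysis section reports 135 randomized so far. 184 − 135 = 49, and 49 / 184 = 27%.

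**The case against.** Several arguments on the other side stand and limit the point.

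- **Coming forward precedes the pack.** Workers volunteer and move to the separate room before they receive it. That step is affected only if the nurse's talk reveals the arm, which the text does not settle. The documented exposure is the decision to sign among people already interested.
- **Eligibility is not tied to the arm.** A reader might infer that the willingness criterion lets the arm decide who is eligible. It does not say that: the criterion is that workers "are interested in participating in a cessation program", which is generic.
- **The sheet is not said to describe the full offer.** A reader might infer that workers know they will or will not have a nurse. The text mentions only log-on or calling information. The letter and consent form are not shown and may describe both programs.
- **The survey's content is only partly stated.** A reader might infer that confidence and perceived difficulty are among the exposed baseline covariates. The Measures section lists these items but does not explicitly place them in the baseline survey. Several listed covariates, such as age, gender and education, are unlikely to move on sight of a handout.
- **The main Aim 1 model hardly uses baseline answers.** It adjusts for clustering, and baseline covariates belong to the supplement. Biased baseline reporting would reach the main result only indirectly.
- **Both arms are active.** Each offers a cessation program, nicotine replacement and a similar number of contacts, which weakens the pull toward one arm compared with an untreated control.
- **Flow by arm may already be planned.** The Design section cites a CONSORT diagram, whose content was not available for this check.

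None of this withholds the arm sheet until after consent, and neither intent-to-treat nor adjustment can recover people who saw it and declined.

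**Conclusion.** The point holds as a defect of procedure. As written, the arm is disclosed before consent and before the baseline survey, which opens a route to selection at signing that the planned analysis cannot fully close.

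The size of any bias is unknown. A reader might infer from the sequence that the arms were recruited differently, or that the primary result is already compromised. The document supports neither, since it gives no enrollment counts by arm. The 2- to 8-point range rests wholly on the assumed quit rates and motivated shares, and smaller gaps give smaller effects. The conclusion itself rests on the stated order of events and on the absence of any statement that the sheet is held back.

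**What to change.** **For the remaining sessions (49 of 184 participants):**

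- Hand out the letter, consent form and baseline-survey instructions first.
- Describe the study in the same words in every session.
- Release the arm-specific instruction sheet only after consent is signed and the baseline survey is submitted.

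**For all sessions:** report by arm the numbers attending, interested and consenting, as far as they were recorded.

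**Analysis:** leave the primary model unchanged, with 135 of 184 already randomized. In the supplementary adjusted analysis, use prespecified baseline predictors that knowledge of the arm is unlikely to alter, such as age, gender and education. A comparison of results before and after the change is not worth adding, because 49 later participants split over two arms would be too few to inform it.

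**Cost:** a minor ethics notification and a few minutes per session. Randomization by session, and the protection it gives against contamination, stay as they are. The 135 already randomized cannot be corrected, and the report should state this limit.
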